### 9.2.5 Stage 4 = Generalisation

Parent counseling is the most frequently used technique during the Generalisation phase. The SLT seeks for topics that the parent(s) is still unsure about or for topics that need more information or training. The parent(s) evolves to an independent speech model for his/her PCWS.

Recovery or low frequency (near zero) and no reactive behaviour over a long period is the goal of Stage 4. The parent(s) and PCWS report that they feel competent and successful to deal with fluctuations in the left-over stuttering, if any.

### 9.2.6 Maintenance phase

The maintenance phase starts when the PCWS and parent(s) achieved the goals of Stage 4. Usually the stuttering is reduced to (near) zero stuttering. Treatment sessions to monitor if achieved goals are maintained are scheduled with an interval of 2, 2, 4, 4, 8, 8 and 16 weeks. If necessary, SLTs add extra sessions during maintenance, for example if the goals were not maintained.

## 9.3 Trial procedures in the LP

All sessions in Stage 1 take 45 to 60 minutes according to the LP treatment guide (Onslow et al., 2021). Sessions of 45 to 60 minutes with parent and PCWS, however, are not reimbursed through the Belgian health care system, only sessions of 30 minutes. Therefore, in this study, one hour sessions were limited to the first six treatment sessions. These sessions are scheduled with one PCWS and his/her parent(s) alone (not in groups). The parent receives education about stuttering and is coached to implement the treatment techniques.

### 9.3.1 Stage 1

Stage 1 aims at reducing the stuttering of the PCWS to (near) zero levels of stuttering (Onslow et al., 2021). During stage 1, parents learn to provide verbal contingencies during daily, 10-minute practice sessions with their PCWS. For unambiguous stutter-free speech, parents can praise, acknowledge the stutter-free speech or formulate a request for self-evaluation to the PCWS. The practice sessions that the parent(s) implement at home aim to give the PCWS the opportunity to practise stutter-free speech. Therefore, activities are specifically chosen and need to be fun for the PCWS. When the verbal contingencies for stutter-free are provided appropriately and effectively, the verbal contingencies for stuttering are also introduced. These are an acknowledgement of the stuttering moment or a request for self-correction. If a PCWS fails to

correct himself, no further verbal contingency on the speech is given (but a praise for the try can be provided).

During Stage 1, treatment sessions are scheduled weekly. The sessions begin with a conversation between the parent (or the SLT) and the PCWS so that the SLT can record a SR (this can also be made based on a recording of the PCWS conversing during everyday life). The SLT then discusses the daily use of the SR-scale with the parent. They focus on stuttering severity and treatment responsiveness during the past week. The parent(s) then demonstrates to the SLT how verbal contingencies were given to the PCWS during the previous week (this can also be made based on a recording). The SLT determines if the parent(s) delivers them in an appropriate way and discusses them with the parent(s). If applicable, they discuss changes to the procedure for the coming week and the SLT models the new (or changed) procedure during an interaction with the PCWS. Then, the parent(s) demonstrates his/her delivering of the new (modified) verbal contingencies and the SLT gives feedback to the parent(s). The SLT concludes the session with a summary of the procedures to be applied for the coming week and discusses them with the parent(s).

Later on, the practice sessions, that the parent(s) implement at home with the PCWS, become more natural and resemble everyday conversations. Also later on in the treatment, a limited number of verbal contingencies are given throughout the day. When the PCWS has typical scores of 0 and 1 on the SR-scale with more 0s than 1s per week for three consecutive weeks, and the stuttering is rated as 0 or 1 during the treatment session, the PCWS can proceed to stage 2.

### **9.3.2** *Stage 2 = Maintenance phase*

The maintenance phase starts when the stuttering is reduced to (near) zero stuttering and parents are able to implement the practice sessions when it is necessary (when stuttering relapses). Treatment sessions to monitor if achieved goals are maintained are scheduled with an interval of 2, 2, 4, 4, 8, 8 and 16 weeks. If necessary, SLTs add extra sessions during maintenance, for example if the goals were not maintained.

## **9.4** *Assessment of compliance*

The SLT will check compliance with a parent compliance checklist that will be generated for each treatment arm (SLT site file). An example can be found in appendix 9.

# **10 SAFETY RECORDING AND REPORTING**

## 10.1 Definitions

Adverse events in this trial are unlikely to occur but may include a significant increase (e.g.,  $\geq 5\%$ SS) of the stuttering compared to baseline measures or a long-term lack of reduction of moderate or severe stuttering (e.g., for 10 weeks).

Serious adverse events, such as the death of a PCWS, are extremely unlikely to be linked to this TreatPaCS as the treatment approaches have no life-threatening consequences.

## 10.2 Recording of safety findings in function of the available evidence

### 10.2.1 *The case of types of intervention that are in routine clinical use*

Increased stuttering indicates that the treatment is not effective. It may harm a PCWS to stutter for a significant amount of time with increased stuttering compared to the baseline stuttering severity (e.g.,  $\geq 5\%$ SS versus the %SS measured by the blinded video analysts in the video recordings of the baseline session) or to have no reduction of the moderate or severe stuttering compared to the baseline session (e.g., over a period of 10 weeks). As a PCWS's awareness about stuttering increases with age, the opportunity to receive treatment that can decrease stuttering successfully decreases with age and a PCWS may develop feelings of anxiety associated with the stuttering if the stuttering persists. Therefore, it is necessary to act when an adverse event is reported.

Mini-KIDS and SCBT are the experimental interventions in this trial. Even though they are not evidence-based as a treatment in their whole, they are practise-based given they are routinely delivered in daily practice. The techniques and procedures that are used in both treatments are evidence-based on their own. Therefore, possible adverse events are known and are limited to the ones listed previously.

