This approach is based on the therapy concept KIDS (‘Kindern Dürfen Stottern’, Sandrieser & Schneider, 2015) for school-aged children and is based on a stuttering modification approach for adults. The main components of Mini-KIDS are supported by evidence. Evidence to support the necessary metacognitive and metalinguistic skills to work directly on desensitization, identification, and modification of stuttering like disfluencies in this young age group by means of pseudo-stuttering is found in several publications, e. g. Arias and Diaz (2010) and Hakim and Bernstein Ratner (2004). Evidence to argue for desensitisation in

treatment for PCWS can be found in Johnson et al. (2010), Karrass et al. (2006) and Prins et al. (2011). For direct work with the modification of speech motor loss of control in young children, evidence is found in research on brain function and motor speech development (e.g., Bohland et al. 2010; Galantucci et al. 2006; Guenther, 2006; Olander et al. 2010). Mini-KIDS as entire program, however, is not yet supported by research-based evidence, only practice-based evidence.

Parents are intensively involved in the three treatment programs.

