### **9.2.3 Stage 2 = Identification**

This stage is only for children of  $\geq 4$  years as it requires sufficient cognitive and auditory skills. The PCWS and the parent(s) identify and discriminate the relevant types of stuttering and the relevant qualities during games with gradual increasing linguistic level. First in the pseudo-stuttering of the SLT, later also in the pseudo-stuttering of the parent and PCWS. In the end, the PCWS identifies real moments of stuttering in his own speech. It is taken care of that there is no new 'sensitisation' (i.e., an increased awareness linked to negative feelings such as concern).

Only relevant types and qualities of stuttering are aimed for: For example, if only repetitions and prolongations are present in the speech of the PCWS and no blocks, only repetitions and prolongations will be identified as type. Once the PCWS can identify and discriminate these types, the quality that hinders communication (duration or tension or both) is introduced as well. Again, tangible tokens facilitate this process (a hard snake and a soft snake for tensed versus easy loose prolongation; long and short snake for prolongation with long duration versus short duration).

The PCWS is ready to proceed to Stage 3 if s/he identifies and discriminates relevant types and qualities of real stuttering in his/her own speech. This does not have to be 100% correct and mainly on long and tensed moments of stuttering.

The parent(s) is ready to move to Stage 3 if s/he easily produces each type of stuttering behaviour in pseudo-stuttering with a positive attitude and discriminate these adequately in the speech of the PCWS.

For the PCWS < 4 years, only the parent(s) learns to identify and discriminate in individual sessions or in a parent group. In this age group, the parent(s) is ready to move to Stage 3 (modification) if s/he easily produces each type of stuttering behaviour in pseudo-stuttering with a positive attitude and discriminate them adequately in the speech of the PCWS.

If by now the stuttering has recovered or only short and easy moments of stuttering remain with declining frequency, there is no modification phase (Stage 3) and CWS and parents move on to phase 4 (generalization).

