#### *11.4.2 Potential effects on health*

Potential effects on health from the intervention on the QOL-measures (EQ-5D-5L proxy 1) are expected to be visible in increased QOL-scores due to increased fluency. In this QOL-instrument, the subscales of “Doing usual activities” and “Feeling worried, sad or unhappy” are the ones of interest.

The estimated outcome in the comparator arm (LP) is “no problems doing the usual activities” and “being not worried, sad or unhappy” in 95% of the children 2 years post-randomisation and in 85% of the children 5 years post-randomisation. The estimated outcome in the experimental treatment arms (Mini-KIDS and SCBT) is also “no problems doing the usual activities” and “not worried, sad or unhappy” in 95% of the children 2 years post-randomisation and in 85% of the children 5 years post-randomisation.

The estimated outcome in the comparator arm (LP) is (near) zero stuttering levels that are maintained in 80% of the children at 2 and 5 years post-randomisation. The estimated outcome in the experimental treatment arms (Mini-KIDS and SCBT) is also (near) zero stuttering levels that are maintained in 80% of the children at 2 and 5 years post-randomisation.

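### Section 10.2.1 closes the adverse event list that 10.1 leaves open, so treatment-related distress without worse fluency would not count as an adverse event

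*Protocol*

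**What the plan says.** Section 10.1 defines adverse events by example: "Adverse events in this trial are unlikely to occur but may include a significant increase" in stuttering over baseline (for instance 5 %SS or more), or a long period, for instance 10 weeks, in which moderate or severe stuttering does not fall.

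Section 10.2.1 argues that Mini-KIDS and SCBT, though not evidence-based as wholes, are in routine use and built from techniques that are evidence-based individually. It concludes: "Therefore, possible adverse events are known and are limited to the ones listed previously".

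Section 10.3 repeats the two events as the triggers for review. Section 10.4 tells the SLT to look for rises or plateaus of stuttering and to record those in REDCap. Section 11.3.3 places the safety analysis in all randomised children and names no other safety variable.

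Elsewhere, section 9.2.3 asks that Mini-KIDS identification should not cause new sensitisation, glossed as "i.e., an increased awareness linked to negative feelings such as concern". Section 1 says that Mini-KIDS as an entire programme "is not yet supported by research-based evidence, only practice-based evidence", and section 3 says that neither SCBT nor Mini-KIDS is evidence-based as a whole.

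**The concern.** Two things do not fit together. The definition in 10.1 is open and the sentence in 10.2.1 is closed, so a therapist cannot tell whether an unlisted event is reportable; 10.3 and 10.4 resolve the doubt towards the closed reading. The closed reading also rests on an inference from the parts to the whole: evidence for single techniques does not establish that the unwanted effects of an untested package are all known.

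At stake is what the safety analysis can show. The trial compares two programmes that lack evidence as wholes with an established one. Both listed events describe a failure to improve overt stuttering, and 10.2.1 says so for the first: "Increased stuttering indicates that the treatment is not effective". A programme that improved fluency but upset some children could therefore finish with a clean adverse event table.

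**Working it through.** No figure in the plan turns on this point, so the check is mainly a comparison of sections.

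**1. Scope of the list.**

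| Section | Scope |
|---|---|
| 10.1 | Open: two examples, each with an illustrative threshold |
| 10.2.1 | Closed: those two and no others |
| 10.3 | The same two, as triggers for review |
| 10.4 | SLT checks for rises or plateaus of stuttering |

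Sections 10.1 and 10.2.1 cannot both stand.

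**2. Does the stated reason support closure?** The premise in 10.2.1 is evidence for components. Sections 1, 3 and 10.2.1 itself concede that evidence for the whole is lacking. The conclusion goes further than the premise.

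**3. Does the protocol foresee anything outside the list?** Yes. The sensitisation in 9.2.3 is an unwanted effect of a treatment step, is emotional, and is neither a rise nor a plateau of stuttering. Section 10.3 also says that the child's response to the stuttering matters, and it lists helping the child with emotions among possible actions. Yet both of its triggers are overt, and it judges the result of those actions by whether stuttering falls further.

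**4. Test case.** Take a child whose stuttering falls during treatment but who becomes distressed or begins to avoid speaking.
- Event 1 (marked increase): not met, since the change is downward.
- Event 2 (no reduction of moderate or severe stuttering): not met, since there is a reduction.
- Adverse events under the closed list: none.

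**5. Overlap with efficacy.** Event 1 is expressed in %SS, the scale of the primary endpoint (4.3.1). Reading the example as a rise of 5 points over baseline:
- against the non-inferiority margin of 1.0 %SS (11.1): 5 / 1.0 = 5.0 times;
- against the assumed SD of %SS at 18 months, 1.7 (11.1): 5 / 1.7 = 2.9 times.

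It is therefore an extreme cut on the efficacy scale. The 1.7 is the SD of a level and not of a change, so the second ratio only indicates scale. Event 2 is absence of benefit on overt severity.

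**6. Where the covert data go.** Section 4.3.2 describes the ISPP, EQ-5D-Y proxy 1 and KiddyCAT as measuring the covert side of stuttering. Figure 3 schedules the EQ-5D-Y at baseline, 3, 9 and 18 months, 2 and 5 years; the ISPP at baseline, 3, 9 and 18 months; and the KiddyCAT at baseline and 18 months. Section 11.3.3 compares these between programmes. Neither section 10 nor the safety line of 11.3.3 uses them.

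**The case against.** The case on the other side has substance.

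**Covert worsening is not invisible.** Section 11.3.3 plans analyses of EQ-5D-Y, KiddyCAT and ISPP, including baseline-adjusted and longitudinal models, first by intention to treat. An average shift towards distress in one arm could appear there. This stands. What those comparisons do not do is count the individual children who got worse.

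**Other channels exist.** At 3, 6, 9, 12 and 18 months the SLT is asked to report risks (8.8.5 to 8.8.9), and Figure 3 has a risk assessment row. Section 8.10.1 mentions a safety checklist, and the flow chart in Appendix 11 is not visible here; either may be wider than section 10. In every arm the fidelity checklist has the SLT observe whether the child is comfortable. A reader might infer that nobody need act for a distressed child, and these provisions contradict that. They do not make distress an adverse event: the comfort item feeds a fidelity score, and a general request to report risks does not displace a sentence that limits the list.

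**The named effects are not all treatment harms.** Section 10.2.1 says "a PCWS may develop feelings of anxiety associated with the stuttering if the stuttering persists", which makes anxiety a consequence of persistence and not of therapy. The child's negative reactions or resistance in Appendix 9 appear as parent compliance items. It would be too strong to say that the protocol lists all of these as harms of treatment; sensitisation in 9.2.3 is the clear case.

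**The safety data are not a copy of the efficacy data.** A reader might infer that they carry no independent information. Adverse events are reported by unblinded SLTs at any time, one of them as a plateau of severity, whereas the primary endpoint is blinded %SS at 18 months. Little is added about harm apart from fluency, which is different from nothing.

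**No count of missed events can be derived.** Section 11.4.2 says that "the subscales of “Doing usual activities” and “Feeling worried, sad or unhappy” are the ones of interest" and expects 95% of children without such problems at 2 years and 85% at 5 years. It is tempting to turn the remainders into missed adverse events per arm. They are expected prevalences, the same in every arm, and not new or treatment-related worsening. The same section expects only 80% to keep near-zero stuttering, so the 5% or 15% could all lie within the 20% who still stutter. The 5-year point also falls after the trial ends at 2 years.

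**Conclusion.** The point holds in a limited form. Sections 10.1 and 10.2.1 contradict each other on whether the adverse event list is open. The closed version is not supported by the reasoning offered for it, and 9.2.3 foresees an effect outside it. As written, the adverse event record adds little about harm beyond the efficacy construct.

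The size is qualitative: the documents give no rate of treatment-related distress, and none should be assumed. Neither the primary analysis nor the sample size is affected. The conclusion rests on the visible text of section 10; a wider definition in the safety checklist or flow chart would reduce the problem to one of wording, but the contradiction would remain. For a cheap change that makes the safety statement more informative, it is worth making.

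**What to change.** 1. **Reconcile 10.1 and 10.2.1.** Replace the last sentence of 10.2.1 so that the two stuttering events are examples and not a limit, and state that new or increased distress, or avoidance of speaking, that the SLT or parent relates to the treatment can be reported on the existing REDCap adverse event form. Align 10.3 and 10.4 with this. What is done about a report stays with the Trial Management Group, as 10.2.2 already provides.

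2. **Add one safety table to 11.3.3.** By arm, in all randomised children with data, give the number and denominator of children
   - whose EQ-5D-Y worried, sad or unhappy level is worse than baseline at 3, 9 and 18 months and 2 years;
   - whose KiddyCAT score is worse than baseline at 18 months.

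   Present it descriptively. The EQ-5D-Y is a proxy report, completed also for children under 4, and children with comorbidities are eligible, so worsening here does not by itself imply that treatment caused it.

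An automatic alert on a worsened questionnaire item is not proposed: it would add a trigger for clinical action with no stated threshold.

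Cost: a wording amendment, one table from data already collected, and some additional low-grade reports for the Trial Management Group to triage.

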### 10.2.2 *General considerations for the recording of safety findings*

Adverse events need to be reported in REDCap by the SLT at any time during the trial (also in between the data collection points). In case an adverse event occurs, the Trial Management Group will decide what type of action needs to be taken. Action can include individualising the treatment approach while still complying to the necessary requirements of the protocol, leaving the allocated treatment arm, or leaving the study. The Co-CI will follow up with the SLT on the decided action.

### 10.3 Expedited reporting of Adverse Events

It is important that the treatment approaches affect the stuttering and the response to the stuttering of the PCWS (and family). A significant increase of the stuttering (e.g.,  $\geq 5\%$ SS) compared to baseline measures or a lack of stuttering reduction of moderate or severe stuttering (e.g., for 10 weeks) are considered to negatively affect the PCWS and his/her family. When an adverse event is reported in REDCap, the Trial Management Group will take a decision about the action that is necessary to take.

Depending on when in the treatment process the adverse event is reported, and depending on the treatment arm, various actions may need to be taken. These may include adjusting to metacognitive skills, checking for desensitisation in the parents, increasing the number of practice sessions or the number of verbal contingencies throughout natural conversations, helping the child manage his emotions or training on increasing the PCWS's speaking skills.

These actions are followed up by the Co-Cis for the next 6 weeks. If these actions are not sufficient to decrease the stuttering further, the Trial Management Group will decide on further action. These may include further individualising of the program, leaving the allocated treatment arm or leaving the trial.

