## 8.10 Withdrawal criteria

### 8.10.1 Discontinuation of trial intervention (without withdrawal of consent)

During the entire treatment phase, the reason and date for drop-out of treatment or the reason, date for leaving the allocated treatment arm are recorded in the e-CRF as well as whether it was the PCWS's, the parent's or the SLT's decision.

Reasons for stopping trial intervention (protocol treatment) may include, but are not limited to:

- ☐ The PCWS and/or PCWS' parent do(es) not wish to continue with trial intervention
- ☐ Safety reasons (Checklist Safety Reporting)
- ☐ Compliance issues of the parent(s). If planned sessions are not attended by the PCWS and parent(s) without a valid reason, it is a compliance issue.

- (1) The SLT may work around holidays or real-life situations in which a PCWS and the parent(s) cannot attend the session for one or more times (eg., illness of a parent, transport issues for some time, ...). These postponed sessions are limited in number and the SLT prepares the PCWS and parent for this gap in treatment.

The PCWS and the parent(s) can miss treatment sessions at most for three consecutive weeks without a valid reason before they are asked to withdraw from the trial intervention.

- (2) The parent(s) are asked to implement the treatment at home. In the Mini-KIDS treatment arm, they agree on their involvement in the mandate. In the LP and SCBT treatment arm, they agree to implement the treatment daily at home for about 10 minutes (LP) or two to three times per week for 20 to 30 minutes (SCBT) for making speaking activities pleasant again. If the SLT records compliance issues that violates those listed in the compliance checklists for each treatment arm, these will be discussed by the Co-CI and CI. It may a reason for discontinuation.

- ☐ Treatment fidelity issues of the SLT

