The video analyst may notice that a SLT adds treatment techniques or omits treatment techniques for the treatment approach that s/he is delivering compared to the treatment fidelity checklists for each treatment arm in this trial. If the SLT does not follow the protocol for more than 80% for a treatment session that was recorded on video, the SLT will be asked to follow the protocol more rigorously. If the SLT does not follow the protocol for more than 80% for each session indicated on the treatment fidelity checklists for more than six sessions, the SLT is considered to drift from the protocolised treatment approach and may be withdrawn from the trial intervention. Because data collection points often have more than a 6-week interval, SLTs are asked to report problems with treatment fidelity.

☐ Other reason

The trial will be analysed on an intention-to-treat basis and per-protocol analysis (Mo et al., 2021). All PCWS who stop randomised trial intervention will remain in the trial for follow-up unless the parent explicitly withdraws consent for data collection.

A PCWS's parent who refuses some or all trial procedures will still be followed up with the data collection procedures that the PCWS's parent(s) is agreeing unless the PCWS's parent(s) explicitly withdraws consent.

If the parent(s) discontinues with the trial intervention and did not withdraw consent, the PCWS will leave the allocated treatment arm or will receive other stuttering treatment than the manualised TreatPaCS treatment approaches from the SLT. The SLT will provide a video recorded speech sample from during the treatment session and from home, and the scores on the KiddyCAT, EQ-5D-Y proxy 1 and ISPP-questionnaire at the set data collection points during the trial after randomisation.

When a PCWS discontinues the trial intervention, a letter to inform the trial procedures for discontinuation will be provided to the PCWS and his/her parent(s). The parent(s) may decide to withdraw consent if s/he is not willing to provide the follow-up data.

The details of discontinuation (reason) should be clearly documented in the PCWS's speech-language therapy file and in the eCRF.

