### ***8.10.2 Discontinuation of study (with withdrawal of consent)***

The parent(s) may withdraw consent at any time during the study. For the purposes of this trial, withdrawal is defined as:

The PCWS and his/her parent withdraw consent from TreatPaCS and are not willing to be followed up for the purposes of the trial at any further data collection points (i.e., only data collected prior to the withdrawal of consent can be used in the trial analysis, no data can be collected anymore from this time point).

The details of withdrawal (reason) should be clearly documented in the PCWS's speech-language therapy files and in the eCRF.

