## 10.7 The type and duration of the follow-up of subjects after adverse events

The decision can be (1) individualise the treatment to the PCWS's needs (2) leave the allocated treatment arm or (3) discontinuation of TreatPaCS. The first action can include a variety of measurements. The duration of the follow-up depends on the action that was taken and will be specified by the Trial Management Group but takes at least 6 weeks.

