| 
The Trial Management Group will decide which actions need to be taken (individualise the treatment approach more within the protocol instructions, leaving the allocated treatment arm or leave the study) and for how long.
                                                                                                                                                                                                                                                                |                                                                     |                                                                                                                                                                                                                                                                                                                                                                                                                           |                  |                 |

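### Section 10 lets the Trial Management Group take a child out of the trial for poor response, an exit that sections 8.10 and 8.11 do not provide for, and does not secure that child's 18-month and 2-year data

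*Protocol*

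**What the plan says.** Section 10.1 gives as examples of adverse events a marked rise in stuttering over baseline (such as 5 %SS or more) and a long lack of reduction in moderate or severe stuttering (such as 10 weeks). The Trial Management Group then decides what to do, and leaving the trial is listed apart from leaving the arm in four places:

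- Section 10.2.2: "leaving the allocated treatment arm, or leaving the study".
- Section 10.3, after a first set of actions and 6 weeks of follow-up by the co-chief investigators: "These may include further individualising of the program, leaving the allocated treatment arm or leaving the trial".
- Section 10.7, after option (1), individualising the treatment: "2) leave the allocated treatment arm or (3) discontinuation of TreatPaCS". The follow-up after the decision "will be specified by the Trial Management Group but takes at least 6 weeks".
- Appendix 1: "leaving the allocated treatment arm or leave the study".

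Section 8.10.1 lists safety among the reasons for stopping the intervention without withdrawal of consent, and rules: "All PCWS who stop randomised trial intervention will remain in the trial for follow-up unless the parent explicitly withdraws consent for data collection". Section 8.10.2 defines discontinuation of the study as the family's own decision: "The PCWS and his/her parent withdraw consent from TreatPaCS and are not willing to be followed up for the purposes of the trial". Section 8.11 recognises three end states for a child: completion with 2-year data, loss to follow-up after three contact attempts, and withdrawal of consent. Its rule for the end of the whole trial uses the same three, plus termination by the sponsor for safety reasons.

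**The concern.** The same child falls under two different rules. Under 8.10.1, a child stopped because of an adverse event is measured to the end. Under section 10, the Group may have that child leave the trial, and no consent decision is mentioned. Section 10 does not say that data collection stops, but it does not refer to 8.10.1 either, and the one duration it sets falls well short of month 18.

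The trigger is poor response on the scale of the primary endpoint, so any resulting gap depends on outcome. It would also be avoidable, because the visits are already planned. The exposed analyses in section 11.3.3 are the secondary outcomes planned first in the intention-to-treat (ITT) population to keep the randomisation intact, the safety analysis in all randomised children, and the ITT and mixed-model analyses of %SS. Carry-forward, the multiple imputation to be explored and the missing-at-random mixed model (11.3.3, 11.3.4) repair such gaps only in part.

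**Working it through.** **The texts side by side**

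| Question | Section 10 and Appendix 1 | Sections 8.10 and 8.11 |
|---|---|---|
| What may follow an adverse event? | Individualise, leave the arm, or leave the study | Stop the intervention |
| Who can end study participation? | Trial Management Group | Parent, by withdrawing consent (or loss to follow-up) |
| How long is follow-up afterwards? | At least 6 weeks, set by the Group | All set data collection points |
| End state of a child removed by the Group | Discontinuation of TreatPaCS | None of the three applies |

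Leaving the study is always listed beside leaving the arm, so it cannot be loose wording for stopping the allocated treatment.

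**Design figures (section 11.1).** Margin 1.0, SD 1.7, one-sided alpha 1.25%, power 90%, true difference 0. Normal approximation: 2 × 1.7² × (2.241 + 1.282)² / 1.0² = 71.7, so 72 per group. With the noncentral t distribution, power at 73 per group is 0.89996, which agrees with the stated 73. Then 73/0.89 = 82.02, so 83 per arm and 249 in total. These figures are not in dispute.

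**Illustration of size.** The protocol gives no removal rate. Assumptions:

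- m = 1, 2 or 4 more children removed in one experimental arm than in LP (1.2% to 4.8% of 83), all of them failures.
- Failure share p = 0.2. Section 11.4.2 expects (near) zero stuttering in 80% at 2 and 5 years; this is assumed to hold at 18 months.
- Failures lie a gap g above the other children. An SD of 1.7 caps g at 1.7/√(0.2 × 0.8) = 4.25. Within-group SDs of 1.0 and 1.2 give √(1.7² − 1.0²)/0.4 = 3.44 and √(1.7² − 1.2²)/0.4 = 3.01. The range used is g = 3 to 4.

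*Success among observed children:* 0.8 × 83/(83 − m) = 81.0%, 82.0%, 84.1% for m = 1, 2, 4, against a true 80%.

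*ITT with carry-forward:* about 0 if the child's level persists. If the 18-month value would have differed from the carried one by 2 points, the shift is 2m/83 = 0.024, 0.048, 0.096 %SS in either direction.

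*Random-intercept mixed model:* simulated with 83 per arm, 17 failures per arm, visits at 3 to 24 months, 18-month SD about 1.6, data of the removed children missing from month 12, 400 runs per scenario. Shift in the 18-month difference, experimental minus LP (negative flatters the experimental arm):

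| Course of the removed children | m = 1 | m = 2 | m = 4 |
|---|---|---|---|
| Unchanged, random failures | −0.011 | −0.019 | −0.040 |
| Unchanged, worst at month 9 | −0.008 | −0.015 | −0.036 |
| Would have worsened by 2 points | −0.033 | −0.068 | −0.137 |
| Would have improved by 2 points | +0.014 | +0.028 | +0.056 |

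*Primary per-protocol analysis, only if removed children still count as at least 80% adherent (11.3.2):* a failure lies (1 − p)g above its arm mean, so the observed difference falls by m(1 − p)g/(73 − m). With SE = 1.7√(2/73) = 0.281, ignoring any variance inflation from the weights, false non-inferiority at a true difference of 1.0 is 1 − Φ(2.241 − shift/SE). Scenario A keeps p = 0.2. Scenario B lets the true difference of 1.0 arise from more failures, p = 0.2 + 1/g, which is 0.533 for g = 3 and 0.45 for g = 4.

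| m | A: fall in %SS | A: false non-inferiority | B: fall in %SS | B: false non-inferiority |
|---|---|---|---|---|
| 1 | 0.033–0.044 | 1.69%–1.86% | 0.019–0.031 | 1.49%–1.65% |
| 2 | 0.068–0.090 | 2.27%–2.74% | 0.039–0.062 | 1.78%–2.16% |
| 4 | 0.139–0.186 | 4.03%–5.68% | 0.081–0.128 | 2.54%–3.69% |

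The nominal value is 1.25%.

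**The case against.** The best reply is that 8.10.1 already governs data collection. It names safety as a cause of stopping and has the therapist supply both speech samples and the questionnaires at the set time points. Section 10 concerns care, and discontinuation of TreatPaCS could be read as the consent withdrawal of 8.10.2. That reading does not hold. Section 8.10.1 protects children who stop the intervention, whereas section 10 lists a separate exit from the study, says nothing of consent and does not point back.

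The other points limit the size of the problem:

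- Section 10.1 calls adverse events unlikely. Section 10.3 reaches the exit only after 6 weeks of other measures, although 10.2.2 and 10.7 list it without that sequence. The Group includes the trial statistician.
- The triggering event is recorded in REDCap before the Group acts, so only later safety data can be lost.
- Every figure above needs more removals in one arm than in the other. With an unchanged course, the mixed model moves by at most 0.04 %SS against a margin of 1.0.
- The success figures assume that removed children drop out of the denominator, which section 11.3.3 does not say. They also use a near-zero stuttering rate for 2 and 5 years in place of the 18-month success definition.
- The 5.7% needs four extra removals, all still counted as adherent, and a true difference exactly at the margin. A child taken off treatment may fail the 80% rule with or without the change.

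**Conclusion.** The concern holds as a contradiction in the protocol's wording. Two sections give different rules for the same child, and following section 10 as written permits outcome-related missing data that could have been collected. The practical effect is probably small and cannot be estimated from the document: no removal rate is given, and the illustrations rest on the assumed excess of 1 to 4 children in one arm, a 20% failure share and a gap of 3 to 4 points. The mixed-model results are illustrative only. The main exposure is in the ITT-based secondary outcomes and later safety data. The primary per-protocol analysis is affected only under the adherence condition. The safety flow chart in Appendix 11 is not shown, so the conclusion rests on the readable text.

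**What to change.** In sections 10.2.2, 10.3 and 10.7 and in Appendix 1, replace the option of leaving the study or trial with: *discontinuation of the trial intervention with continued data collection as in 8.10.1*. Add one sentence to section 10: *Only the parent's withdrawal of consent, or loss to follow-up, ends a child's data collection before 2 years; the follow-up of at least 6 weeks in 10.7 does not replace the 18-month and 2-year data collection.* A cross-reference alone would help, but it would leave the four conflicting phrases in place.

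The cost is wording only. Follow-up is already planned for every child, no sample-size figure changes, and the Group keeps its freedom over the child's care. The one downside is that some families whose child did poorly will still be asked for recordings and questionnaires.
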